## Prototype intervention

Table 2 summarizes the range of cognitive constructs and training objectives that could be addressed by a mobile app. When one considers that it takes sustained practice to acquire mastery of any of the elements in the last column of Table 2, it becomes evident that the range of training targets is far too large for any app. Our review of sports-related apps currently on the market suggests that most of them are modest in their offerings. They provide feedback on a narrow range of biomarkers and/or they concentrate on a limited range of skills (e.g., controlled breathing). Faced with this same dilemma for the initial version of our app, we decided to develop web-based resources that users could consult to gain a better understanding of psychological skills underpinning high performance and how they can be trained using the app. These web-based resources are more than an optional add-on, they form an essential component of the intervention, and will be described next.

### Building the app: Web materials

The CF2 App is supported by a website designed to provide additional support for the study participants. This support takes the form of:

an educational video used as a pre-briefing to the app-driven training program, looking at developing a “High Performance Mind Set,” establishing a strong “Self-Belief,” and better understanding of “Attentional Control;”an educational video covering skills involved in the training program;additional reading expanding on the skills involved in the training program;additional reading providing contextual case studies of athletes being challenged in competition to use the skills involved in the training program.

There are ten pages on the website. The Home page provides a simple “concierge” function that provides participants with direct links to the pre-briefing videos referred to in their introductory correspondence.

The second page introduces the Cognitive Fitness Framework. The messages and definitions are provided in a language system that is compatible with the app and the pre-briefing videos. It provides participants with logical progressions of the concepts behind the training program.

The third page carries the title “How This Works,” and it provides an explanation of how the app and the website work together. It provides a “Road Map” of where the participants should go for various aspects of the study.

Page 4, headed “Elite Systems,” has two sub-pages: “Standard Practice Routines” and “Manage Your Mental Health.” This section provides information on the skills, attitudes, and capabilities that individuals with strong cognitive fitness evidence. It also explains the basis of the routines and origin of the systems behind the training program structure. The section also addresses the links between “Cognitive Fitness Training” and mental health management.

Page 5, headed “Briefing,” has four key sub-pages, and additional topic support sub-pages. The key sub-pages are:

“Mind-Set and Self-Belief Principles Embraced by Elite Performers.”“Mind-Set and Self-Belief Background Material.”“Attention Control Principles Embraced by Elite Performers.”“Attention Control Background Material.”

The additional topic support sub-pages include “Imagery,” “Relaxation,” and other areas that sub-tend some of the drill structures.

The key sub-pages referring to principles embraced by elite performers contain the pre-briefing video material that participants are required to interact with before commencing their training program *via* the app.

Page 6 is headed “Definitions,” and contains a glossary of terms used both in the Website and the app. It is designed to facilitate participants progressing through their training program with an unambiguous explanation of key concepts.

Page 7 is headed “References,” and contains a systematic collection of links to additional materials and sites relating to the concepts contained in the website and the training program contained in the App.

Page 8 is headed “Stories” and contains case study examples of athletes requiring or using the skills developed in the training program. These case studies inform participants’ understanding of the relevance of the drills that comprise the training program.

The last page is headed “More.” It contains links to other resources, such as papers, infographics or talks on topics of interest to those seeking to improve performance or overall wellbeing. Examples include special breathing techniques, heart rate variability, performance debriefing, and how to better cope with the lifestyle demands of performing in high expectation environments.

Although the website adds some further resources for those looking for ways to improve wellbeing and performance, at its core are the pages supporting the app, which we will now describe.

### Cognitive gym: Target behavioral outcomes

A number of decisions had to be made before work could start on the app. Moving some of the supporting material to the Web was the first of those decisions. Deciding not to offer biofeedback in the first version of the app was the second decision. The most difficult decisions, however, concerned the choice of cognitive abilities and associated drills to include. To help with that task, we drafted a set of expectations of high performers that was consistent with the CF2 model. Those expectations are shown in Figure 2.

**Figure 2 fig2:**
[figure not shown]
Functional capabilities of high performers (adapted from Crampton et al., 2021).

Figure 2 provides verbal descriptions of behaviors that we are seeking at various stages of the performance cycle. To select from the many construct/drill combinations that are available, we then devised a filtering system that we could apply to any drill (Crampton et al., 2021). The first step of this filtering system involved what we call a “first-glance” evaluation of the drill where we examined its broad qualities, such as whether it was suitable for inclusion in an app. The second step applied a more stringent cause-and effect evaluation to check whether the drill is supported by research. The third step considered whether the drill could produce reliable and valid measures of the construct it is developing. The fourth step considered the availability and quality of instructions for the drill. Do these exist? Are they adequate? If not, can they be developed in a form that will suit the app? If the drill passed through each of the filters, it became a candidate for inclusion in the app. The same filtering system can be applied to constructs as well as drills, even those selected from the CF2-based Table 2.

After selecting the drills for inclusion in this prototype, the next decision related to ways of presenting them. Options included stand-alone drills or combinations of drills in the form of loops or sequences. A concentration drill, for example, may be interspersed with breathing exercises, in much the same way that an athlete would be expected to use combinations of drills in training and competition settings.

### Cognitive gym training program: Practice drills

The initial version of the app was designed to satisfy a “proof of concept” requirement for the project. For this purpose, the selected drills were combined into a single intervention to form a Cognitive Gym. The intervention employs a blended delivery methodology, combining face-to-face pre-brief with a three-week program *via* a web application that is designed to help participants exercise their primary cognitive capacities and performance-focused cognitive skills. The web application contains educational videos, guided cognitive workouts, breathing sessions, user engagement tools, completion trackers, leaderboards, and a social feed. The Cognitive Gym also uses gamification techniques to consolidate behavior change.

The current prototype (see Supplementary material S2, panels A,B) contains a recommended sequence of 2 h of instructor-led learning followed by one-and-a-half to 3 weeks of 30-min daily practice. This core sequence includes:

Program “brief in” introducing the intervention as “cognitive fitness training” similar to conditioning and skill training work. Included in the briefing is an education section on developing a “high performance mindset” and on developing understanding and control of attentional flexibility. Participants will be encouraged to apply their knowledge of those areas to their cognitive fitness work. This two-hour instructor-led instruction was accomplished by preparing a set of eight introductory videos promoting the use of the app to achieve a high-performance mindset. The additional Web resources described earlier are also available to the trainee.Daily 30 min practice involves ten sequential drills, guided by a mobile device-based app with built in engagement functionality to encourage participants’ continued involvement. The ten drills are described below.

External attentional flexibility: Participants are guided to utilize the camera on their mobile device to rapidly shift their focus from narrow to medium to broad external awareness of their surroundings for 45–60 s.CubeRunner 2: simulated aircraft flight through congested, distracting airspace. Participants are instructed to maintain a flexible external focus of attention for extended periods on a gamified cognitive control task, notified by a three-minute countdown timer. This task is illustrated in Supplementary material S2 (panels D and C).Do not be in a hurry to breathe: Participants are guided through a breath-based relaxation induction followed by a challenge to reduce breathing rate to the lowest comfortable cadence and sustain the pattern for a string of ten breathing cycles focused on slow and smooth transitions from exhale to inhale. The drill finishes when focus is lost, after which the participant completes the remaining attempts as practice, and is then guided through a breath-based “wake up” exercise returning awareness and breathing to baseline.Color timer: Participants maintain an extended narrow external focus of attention and respond by tapping a colored dot matching a color dot stimulus in a three-choice reaction task. Stimulus presentation is repeated in an ongoing random sequence with a specified time limit for each response. Missing the allowed time finishes the trial, resulting in a string score (number correct within time in a row). The aim is to produce a new personal best string each trial. Multiple trials are permitted within the allocated drill time. A countdown timer is used to advise of the end of the 3 min of training.Getting centered: Participants are guided through a sequence of thoughts and feelings that build a sense of control of their center of gravity—incorporating postural and specific breathing instructions.Higher lower: Participants complete a simple numeric operation on screen and respond by swiping the screen up or down to indicate whether the result of their calculation is higher or lower than the number previously presented on screen. The response is timed as well as scored for accuracy.Empty headed: Participants are guided through an imagery-based relaxation induction followed by a sequence of trials where they attempt to “let go” of distracting thoughts across varying periods of time. The time periods are directed by an audio recording. The three-minute drill concludes with an imagery-based “wake up” exercise.Red square: A three-minute collision-avoidance task where participants are required to maintain a flexible external focus in order to move their avatar (a red square) away from three randomly moving blue squares. The aim is to improve personal best scores (expressed in seconds) across each trial. Multiple trials are permitted within the allocated training time. The end of the training period will be notified by a countdown timer.Imagination sequence: Participants will be guided through a three-minute sequence of imagery training drills. The sequence commences with a loop of generic drills, and then progresses to a sequence of imagery drills related to aspects of their training or competition performances.Attentional spiral: Participants will be guided through a three-minute sequence of attention shifts that move from generic to personally relevant cues, and then they are assisted to transition to their ongoing daily challenges.

The drills are the building blocks of the Cognitive Gym. They will be administered either alone or in combination (e.g., imagery drills preceded by breathing drills). Combinations comprise as many as five different drills arranged as loops, sequences, spirals, or other sequences. Each drill involves systematic and disciplined execution of underpinning cognitive skills, such as concentration, endurance, and attentional flexibility. The core instruction is delivered *via* the smartphone mobile app (see Supplementary material S2, panels A and B) and backed by the companion website described above, which offers extensive background information and additional practice options.

## Evaluating the cognitive gym prototype: Methods

It is important to evaluate the prototype app in the context of a well-defined Cognitive Gym training package catering for a well-defined user group. The current proof-of-concept study will evaluate the app-supported Cognitive Gym training package in a sample of competitive athletes. The evaluation will assess training gains and participants’ engagement with the app. More details are given below.

### Participants

A total of 60 participants will be drawn from national training squads using the project team’s coaching contact lists (see sample size calculations in “Planned analyses”). All members of the selected training squads aged between 18 and 30 years will be invited to participate but they will be free to decline or withdraw at any point without any adverse consequences. Younger athletes will be excluded from the current study, with a separate study planned to address this age bracket. Participant IDs will be issued to all consenting athletes. The dataset will include demographic data including age, gender, sport and functional role, but it will contain no personally identifiable information.

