### Study design

A cross-over design was chosen for this study as it improves statistical power by making each participant a baseline for themselves. It is also driven by the need to achieve sufficient buy-in from the participants and their coaches—the groups known for their dislike for passive control designs where participants in control conditions can miss out on the potentially beneficial intervention.

In our cross-over design participants will be randomly assigned to either a “training-first” or “waiting first” group. All participants will complete baseline assessment using methods (described in “Outcome measures”) at the start of Week1 (Time 1), then repeat it at the start of Week 4 (Time 2) and at the completion of Week 6 (Time 3). A single blind strategy will be utilized, with researchers administering pre- and post-assessments having no access to the information on which group the participants belong to (training-first or waiting-first).

Following Time 1 assessment, the “training-first” group will commence the three-week training program described in Section 3.3 above, spending 30 min a day practicing the drills delivered through the Cognitive Gym app. The “waiting first” group will have no engagement with the Cognitive Gym app for the first 3 weeks but will have access to the companion website for the designated 30 min daily. They will commence their three-week training with the app immediately after Time 2 assessment. Access to the app will cease for the “training-first” group after Time 2. As a result, each participant will go through 3 weeks of Cognitive Gym app-supported training and 3 weeks waiting, with half of them randomly assigned to training first and then waiting, and the other half—to a reverse order. Coach ratings of athlete progress will be examined in the evaluation, so their consent to participate will also be sought.

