#### Coach ratings

Coach assessment of “far transfer”: to ascertain the extent of training gains transfer to the sporting contexts, athletes will be rated by their coaches. Coach ratings assess the athlete’s attributes such as composure in competition (e.g., 1 = cool, 2 = calm, 3 = worried, 4 = flustered) and adaptability (e.g., 1 = rigid; 2 = gets stuck; 3 = flexible; and 4 = fully adaptive). More details are in Supplementary material S1.

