### Planned analyses

It is expected that, with practice, participants will improve their performance scores on the respective drills. These changes will be monitored and evaluated throughout the intervention. A single blind strategy will be utilized, with researchers administering pre- and post-assessments having no access to the information on which crossover group the participants belong to (training-first or waiting-first).

Improved scores on the drills, however, is no guarantee that participants have learned skills that transfer to similar cognitive tasks (i.e., near transfer), such as the working memory, response inhibition, and cognitive flexibility tasks included in the CogMission battery. Near transfer effects will be evaluated by estimating training gains defined as differences between each CogMission measure at baseline and at the end of the Cognitive Gym training.

Repeated measures ANOVA and mixed linear modelling will be used to estimate effect sizes. Effect size of *d =* 0.4 on training-induced change is considered meaningful and practically important, based on a meta-analysis of randomized controlled trials examining the effects of similar programs on stress (Dhir et al., 2021). This effect size corresponds to *f =* 0.25 for ANOVA power calculations. To reliably detect effects of this size, with two groups and three repeat measurements in our design, G*Power calculations return a minimal sample size of 28 participants (Faul et al., 2009). Allowing for sample attrition and the uncertainty associated with extrapolating power calculations for mixed linear modelling, this study will aim to recruit 60 participants.

Far transfer effects will be evaluated through the coach and athlete ratings. Despite some well-known limitations of self-reports, they have advantages such as easy interpretability, information richness, and practicality (Paulhus and Vazire, 2009). Similar ANOVA and mixed linear modelling will be applied to assess training gains on these measures. Evidence of both near and far transfer effects will address the frequently-voiced objections that gamification techniques lead to improved performance in the games themselves but not in the broader skills they are meant to develop.

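### Athletes come through squads and are rated by their own coaches, but allocation and analysis are described without squad: a minor, cheaply avoided loss of efficiency, not a bias

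*Protocol article*

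**What the plan says.** Recruitment (Participants): "A total of 60 participants will be drawn from national training squads", and "All members of the selected training squads aged between 18 and 30 years will be invited to participate". Members may decline. The number and size of squads are not given. The demographic items listed include sport and functional role, but not squad or rating coach.

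Allocation (Study design): "participants will be randomly assigned to either a “training-first” or “waiting first” group", "with half of them randomly assigned to training first and then waiting, and the other half—to a reverse order". The unit is the athlete. The cross-over is justified because it "improves statistical power by making each participant a baseline for themselves".

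Far transfer (Coach ratings): "athletes will be rated by their coaches". The example items are four-point scales. That one coach rates a whole squad, and the same athletes each time, is implied rather than stated.

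Analysis (Planned analyses): "Repeated measures ANOVA and mixed linear modelling will be used to estimate effect sizes", and similar models are planned for the coach and athlete ratings. The power calculation has two groups measured three times and gives a minimum of 28. This is raised to 60 for attrition and for the uncertainty of carrying the calculation over to mixed models. No squad or coach factor appears in the description.

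**The concern.** Athletes in one squad share a sport, a training load, a competition calendar and probably a rater. If squads change differently between Time 1 and Time 3, two things follow when squad plays no part in allocation or model.

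- The between-squad part of the change stays in the residual variance, so the test is less precise than it could be.
- By chance, one sequence can hold more athletes from a squad that is improving, or whose coach is becoming more lenient. This adds noise to the comparison, most plausibly for the coach-rated far-transfer outcome.

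Precision is what is at stake. The model can be amended later, but stratification has to be settled before allocation starts.

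**Working it through.** **1. The plan's own figure.** For the repeated-measures interaction test, λ = f²·N·m/(1−ρ). With f = 0.25, N = 28 and m = 3 from Planned analyses, and ρ = 0.5, α = 0.05 and sphericity assumed, λ = 0.0625 × 28 × 3 / 0.5 = 10.5 on 2 and 52 degrees of freedom. Power is 0.812, so 28 is reproduced. Nothing below changes that number.

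**2. Constant coach severity.** Null simulation: 60 athletes, 3 or 6 squads, severity SD 0.5 against a within-squad rating SD of 1, 4,000 runs per scenario, unstratified 30:30 allocation.

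- Mean severity differs between sequences by chance only: mean about 0, SD 0.10 (3 squads) and 0.12 (6 squads).
- The SD of the between-sequence difference in change is 0.257 and 0.258 with severity, and 0.257 and 0.263 without it. Severity cancels.
- A separate run gave squad a stable share of 0.1/0.2/0.3 of the rating variance (five squads of 12, within-athlete correlation 0.5). Power for change was 34/33/34% unstratified without a squad term and 32/34/32% stratified with one: no gain.

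**3. Squad-specific drift.** Adding a squad drift in change of SD 0.33 to 0.5 raises the SD of the difference to 0.266–0.281 without stratification, against 0.258–0.260 with it. That is a 2–9% larger standard error. Type I error without stratification, over all scenarios in steps 2 and 3, stays at 0.046–0.055.

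**4. Size of the gain.** Assumptions: five squads of 12, 30 athletes per sequence, one change score with total SD 1, d = 0.4, squad share s of the variance of *change*. With stratification and a squad term, the variance of the difference is (2/30)(1−s), on 60 − 5 − 1 = 54 degrees of freedom.

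| s | Noncentrality 0.4/√[(2/30)(1−s)] | Power with fix, by formula | Simulated: no squad → with fix |
|---|---|---|---|
| 0 | 1.549 | 33% | no gain |
| 0.1 | 1.633 | 36% | 33% → 36% |
| 0.2 | 1.732 | 40% | 35% → 39% |
| 0.3 | 1.852 | 44% | 36% → 44% |

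In information terms, the ratio is at most 1/(1−s): 60 athletes count as up to 60/0.9 = 66.7, 60/0.8 = 75.0 and 60/0.7 = 85.7. With only five squads the unadjusted variance averages (1−s) + s × (4/5) × (60/59). At s = 0.3 this is 0.700 + 0.244 = 0.944, so the ratio is 0.944/0.7 = 1.35 rather than 1.43.

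The power *levels* here belong to a single between-sequence contrast in units of the SD of change. They should not be set against the 28 in step 1; only the differences matter.

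**5. Stratifying without the term.** At s = 0.3 the true variance factor is 0.7. The unadjusted model estimates on average [4 × (12 × 0.3 + 0.7) + 54 × 0.7]/58 = 55/58 = 0.948. The standard error is therefore too large and the test conservative. Simulated type I error at s = 0.1/0.2/0.3 was about 4.3/3.3/2.0% in one run and 4.0/3.4/2.7% in a run of 20,000 trials per cell.

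**6. Chance imbalance.** With exactly half of 60 in each sequence, a squad of 12 splits 8:4 or worse with hypergeometric probability 33%. Independent coin tosses would give 39%, but the plan specifies halves.

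**The case against.** The strongest reply is that this is silence in a condensed article. Stratification factors and model terms are often left to the full protocol or SAP, and Planned analyses names mixed models, which could carry a squad or coach effect. That stands as far as it goes: the article does not say squad will be left out, and omission of such detail is not itself a fault. The point is worth making because the article's own recruitment and rating arrangements create the clustering, and the allocation step cannot be redone.

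Three stronger readings are tempting, and the documents support none of them.

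- *Coach severity biases the far-transfer result.* Athletes are randomised individually, so squad imbalance is random. Coach ratings are analysed as gains, so constant severity drops out if the rater stays the same. It would matter only for raw post-training scores or a change of rater.
- *Sixty athletes are worth far fewer because of clustering.* The design effect 1 + (m−1)·ICC applies when squads are randomised. For squads of 12 and ICC 0.1 it would be 1 + 11 × 0.1 = 2.1, but here both sequences can occur within a squad and that inflation does not arise.
- *A squad main effect in the repeated-measures model is enough.* It absorbs stable level differences, which already cancel, and leaves squad-specific change in the error.

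It is also fair that squads are not recruited whole: only consenting members aged 18 to 30 take part.

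**Conclusion.** The point holds as a minor matter of efficiency. The comparison as described is valid: no bias, and simulated type I error of about 4–6%. What can be lost is precision, and only if squads differ in how they change over the six weeks. Under the assumed five squads of 12, the gain from the fix at d = 0.4 is nil at a squad share of 0, about 3 points of power at 0.1, 4 at 0.2 and 8 at 0.3. The number and size of squads, the squad share, and one constant coach per squad are all assumptions; the article gives none of them. The minimum of 28 and the target of 60 are unaffected.

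**What to change.** - Record squad and rating coach for every athlete and assessment, and state whether the same coach rates at all three times.
- Stratify the sequence allocation by squad, for example with permuted blocks within squad, so that each coach rates athletes in both sequences.
- Include squad by time in the repeated-measures ANOVA and mixed models, or squad as a factor where change scores are modelled. Do this together with the stratification, because stratification alone makes the test conservative.
- For coach ratings, add a sensitivity analysis of whether the training effect differs between squads.

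If allocation has already taken place, the model term alone is still useful at the larger shares. With a 30:30 split and five squads, unstratified allocation gives up on average (5−1)/(60−1) = 6.8% of the information once squad is adjusted for, so little or nothing is gained at a share of 0.1.

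The cost is a stratification factor in the randomisation list, a model term and about four degrees of freedom (58 to 54 in the change-score model). The benefit is negligible if squads do not differ in change.
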